### 2.11. Statistical Analyses

Data were analyzed using SPSS Statistics version 26. Immediate and chronic stress were assessed with psychological subjective indicators of stress and physiological markers of stress. Descriptive statistics (mean, standard deviation, range) were calculated for demographics, the PSS, and VAS scores for all time points. Power calculations were computed. In addition, we reported effect size estimates. The distribution was assessed, and if needed, data were log-transformed to be normally distributed accordingly, especially since cortisol and SAA data may have a positively skewed distribution.

The effect of repeated music interventions on chronic stress was measured with the biomarker HC. HC concentrations were reported in pg/mg. Concentrations of HC at baseline were assessed as a predictor of treatment response. In order to assess the association between the HC concentration and perceived stress (PSS-10), correlations were computed. Changes in HC concentrations over time and perceived stress (PSS-10) were assessed. The levels of stress after 3 and 6 months were modeled to account for differences in therapy: RCS compared to control (usual care or book reading), GMT to control, GMT + RCS, and baseline differences in stress (T0). In the final model, in which MADRS scores at the endpoints (3 and 6 months) were predicted by the therapy group, baseline stress was added to observe whether there was a change in treatment effect. The analyses included a correlation between stress reduction (at T3, pre-post treatment) and change in MADRS score (T6–T3–T0).

SC and SAA were concomitantly measured and were used as outcome measures to assess whether changes in activity in the HPA axis and the ANS axis occurred pre- and post-intervention. Pre- and post-sampling weight of saliva samples were measured. Levels of SC were reported in nmol/L and levels of SAA in U/mL. Adherence to instructions prior to the collection of the saliva sample was assessed. A description of the effect of SAA response (expected to change at 15 min) and SC response (expected to change at 60 min) was provided. The design is able to account for between-group variation (including differential responses in four groups) and within-group variation (changes in participants between 3months, 6 months, and baseline). Exploratory subgroup analyses and moderator analyses were performed.

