Biomarkers are increasingly used to investigate the potential stress-reducing effect of listening to music and music-making [16,26,27,28,29]. However, so far, relatively little research has been conducted to assess the effect of music-making on biomarkers, such as cortisol levels, in people with dementia and/or depressive symptoms.

The primary objective of this study was to assess the effect of repeated music interventions on chronic stress in care home residents with dementia and depressive symptoms. The differential effect of RCS, GMT, and RCS plus GMT was compared to care as usual. Secondary objectives were to assess whether the baseline level of chronic stress, as indicated by HC, is a predictor of therapy outcome (reduction in depressive symptoms) and to assess the immediate effect of music interventions on stress. As high depression scores correlate with higher HC concentrations, we hypothesized that participating in a music intervention would result in lower HC concentrations, with greater changes in the intervention groups than in the control group. The design of this study meets requirements to tackle frequent limitations in studies of HPA axis and/or ANS activity in music interventions in people with dementia, given the intervention duration, repeated assessments, control group for comparison, assessing both immediate and longer-term intervention effects [30].

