### 2.9. Sample Size and Power

Through convenience sampling, a subsample of residents from three countries (the Netherlands, Germany, and Norway) from the MIDDEL trial was asked to participate in this substudy. The aim was to include 50 care home residents in every group (GMT, RCS, GMT plus RCS, control group at baseline). The Netherlands and Germany aimed to include 8 CHUs/80 participants each, and Norway aimed to include 4 CHUs/40 residents. Attrition of residents was expected to occur due to mortality, moving to another care home, or refraining from participation in the substudy. The mean length of stay in a care home in the Netherlands is 8 to 12 months. A mortality rate of 20% within the intervention period of 6 months (primary outcome at 6 months) was taken into account with respect to the sample size. Mortality is lower in care home residents with mild to moderately severe dementia (compared to severe and very severe). The power for this exploratory substudy with this given sample size was difficult to determine because there are no previous studies or agreed minimal clinically important difference for this combination of intervention, population, and outcome. As in the MIDDEL protocol [1], the main effects in this substudy were tested as GMT versus no GMT and RCS versus no RCS so that all participants with available data could be used in each test. Thus, after a dropout of 20% until the primary endpoint of 6 months, as assumed in the MIDDEL protocol, we expected to have 160 participants in total. Compared to the MADRS, we expected the cluster effect in these biological indicators to be smaller, with an ICC ≤ 0.01. The average cluster size after 20% dropout will be eight. Because there are two main comparisons, tests were Bonferroni-corrected from 5% to 2.5%, two-sided. We used R to determine the effect size for which 80% power is reached with a two-sample *t*-test with 160 participants in total, adjusted for clustering, with a two-sided 2.5% significance level, and found that the effect size that can be reliably determined with this substudy is d = 0.51, i.e., a medium effect size [51]. This seems reasonable compared to previous studies of music therapy [14,52]. The actual power may be higher in a longitudinal model if time points are correlated.

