### 2.10. Data Analysis

#### 2.10.1. Co-Primary Study Parameters

Stress (HC concentrations and perceived stress measured with the PSS-10) after 3 and 6 months was modeled to account for differences in therapy (RCS compared to no RCS, GMT compared to no GMT, additional effects of GMT + RCS combined, and baseline differences in stress (HC concentrations and perceived stress measured with the PSS-10) (T0).

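### Section 2.11 and the stated objective compare single arms with control, but the d = 0.51 in Section 2.9 holds only for the factorial margins (GMT vs no GMT, RCS vs no RCS)

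*Protocol article*

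**What the plan says.** Four places in the protocol article describe the treatment contrasts.

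- **Section 2.9 (Sample Size and Power):** "the main effects in this substudy were tested as GMT versus no GMT and RCS versus no RCS", chosen "so that all participants with available data could be used in each test". The section counts two main comparisons, tests each at a two-sided 2.5%, and reports d = 0.51 as the effect detectable with 80% power.
- **Section 2.10.1 (Co-Primary Study Parameters):** stress at 3 and 6 months is modelled on "RCS compared to no RCS, GMT compared to no GMT, additional effects of GMT + RCS combined", together with baseline stress.
- **Section 2.11 (Statistical Analyses):** the same model, with the same outcomes, time points and baseline term, is described as "RCS compared to control (usual care or book reading), GMT to control, GMT + RCS".
- **Section 1 (Introduction), with the primary objective:** "The differential effect of RCS, GMT, and RCS plus GMT was compared to care as usual".

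Section 2.5 gives the book-reading sessions to residents of the standard-care group. The bracket in Section 2.11 therefore points to the control arm.

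**The concern.** The comparator for RCS in Sections 2.9 and 2.10.1 is everyone not offered RCS, which pools the control arm and the GMT-only arm. In Section 2.11 and in the objective it is the control arm alone. These are different quantities. Write s for the effect of GMT alone against control, and δ for the amount by which the GMT effect changes when RCS is also given. The single-arm contrast is s. The margin averages s and s + δ, which is s + δ/2. If δ is zero the two agree in value and differ only in precision; otherwise they differ in value as well.

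The precision also differs. A margin uses all four arms and a single-arm contrast uses two. An analyst who follows Section 2.11 would be testing something for which the article gives no detectable effect, while the Conclusions describe the study as having enough power without saying for which contrast. With both versions in print, either set could later be presented as prespecified.

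**Working it through.** **Inputs, all from Section 2.9**

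- "The aim was to include 50 care home residents in every group": 4 × 50 = 200 at baseline.
- Dropout of 20% by the 6-month endpoint, leaving 160 residents overall: 200 × 0.8 = 160. Assuming equal arms and equal dropout, this is 50 × 0.8 = 40 per arm and 80 per side of a margin.
- Intracluster correlation: "with an ICC ≤ 0.01"; the upper bound 0.01 is used.
- Average cluster size after dropout 8; two-sided 2.5%; 80% power; two-sample t-test adjusted for clustering.

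**Formulas**

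- Design effect: 1 + (8 − 1) × 0.01 = 1.07.
- Effective size per group: nₑ = n / 1.07.
- Power: probability that a noncentral t with 2nₑ − 2 degrees of freedom and noncentrality d × √(nₑ/2) exceeds the two-sided critical value. The detectable d is where this equals 80%.

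**Step 1: reproduce the stated figure.** For a margin, nₑ = 80/1.07 = 74.8. The detectable d is 0.509, and power at d = 0.51 is 80.2%. The normal approximation gives (2.241 + 0.842) × √(2/74.8) = 0.504. The stated 0.51 is correct for a margin.

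**Step 2: apply the same method to one arm against control.** Here nₑ = 40/1.07 = 37.4. The detectable d is 0.726; the normal approximation is 3.083 × √(2/37.4) = 0.713. At d = 0.51 the noncentrality is 0.51 × √(37.4/2) = 2.2, and power is 47.0%.

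**Step 3: vary the assumptions.**

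| Contrast | Two-sided level | Detectable d | Power at d = 0.51 |
|---|---|---|---|
| Margin, 80 vs 80 | 2.5% | 0.51 | 80% |
| Single arm vs control, 40 vs 40 | 2.5% | 0.73 | 47% |
| Same, residual df pooled over four arms | 2.5% | 0.72 | 48% |
| Same, no multiplicity correction | 5% | 0.66 | 59% |
| Same, three comparisons (objective only) | 1.67% | 0.76 | 41% |

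With 180 residents recruited, the lower end in Section 2.2, 180 × 0.8 = 144 are analysable. The 2.5% figures are then 0.54 for a margin and 0.77 for a single arm. To detect d = 0.51 with 80% power in a single-arm contrast at 2.5% would take about 80 analysable residents per arm, or about 320 in four arms.

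**Step 4: the combined effect.** The GMT × RCS term is a difference of two differences, with four cells of 40. Its standard error is √(4/nₑ), against √(2/(2nₑ)) = √(1/nₑ) for a margin, with nₑ = 37.4 in both. The ratio is 2, so the detectable interaction is about 2 × 0.509 = 1.02.

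**The case against.** The strongest reply is that the article does settle the matter. Section 2.9 is the only place that deals with testing, significance level and power. It names the two main comparisons, gives the reason for them, and Section 2.10.1 repeats them under the co-primary heading. Section 2.11 follows 2.10.1 in content and order, so it may be a loose paraphrase. The Introduction speaks of comparing, not testing. The study is also called exploratory throughout, and the article admits that power was hard to determine.

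Much of this stands, and it rules out several stronger readings that a reader might infer:

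- **That no passage designates the main contrasts.** Section 2.9 does.
- **That d = 0.51 was miscalculated.** It reproduces for the contrasts it is attached to.
- **That Section 2.11 sets out three arm-vs-control tests, so that a Bonferroni factor of two is wrong there.** Section 2.11 gives the combination arm no comparator and assigns no significance level. Three comparisons with usual care appear only in the objective, and the mismatch with the two-comparison correction arises only if that set were confirmatory.
- **That the combined-effect term in Section 2.10.1 itself throws away the factorial gain.** This would follow if the GMT and RCS coefficients under 0/1 coding were taken as the primary effects. No coding is stated, and the section labels its terms as comparisons with no RCS and no GMT. Under −0.5/+0.5 coding in a balanced design the margins keep their full precision with the term in the model. This is a caution about coding, not an error.

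The paraphrase defence does not fully succeed. The bracket in Section 2.11 identifies one arm, and pooled no-RCS units are not all usual-care or book-reading units. The objective names the same comparator. An exploratory label does not remove the difficulty either, because the article names co-primary outcomes, corrects for multiplicity and claims sufficient power. The possible gain from a longitudinal model is real but unquantified, and it would benefit both sets of contrasts.

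**Conclusion.** The inconsistency is real. Sections 2.9 and 2.10.1 agree on margins; Section 2.11 and the objective use the control arm as comparator. The stated d = 0.51, and with it the power claim in the Conclusions, applies to the margins only. For a single arm against control the detectable effect is about 0.73, and power at 0.51 is about 47%.

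The figures assume equal arms of 40 after 20% dropout, an intracluster correlation of 0.01, clusters of 8, and the article's own t-test method. Because they leave out baseline adjustment and repeated measures, 47% is not the power of the planned model. The loss relative to the margin, from using half the residents, remains.

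**What to change.** 1. In Section 2.11, replace the arm-vs-control wording with the margins of Sections 2.9 and 2.10.1, and state that these are the only two primary contrasts, each at a two-sided 2.5%.
2. Label the arm-vs-control comparisons and the combined GMT × RCS effect as secondary, with detectable effects of about 0.73 and about 1.0 at the 2.5% level.
3. Reword the objective in the Introduction to match.
4. In the Conclusions, limit the statement about power to the two margins.
5. Keep the combined-effect term in Section 2.10.1 if wanted, and state that the primary GMT and RCS effects are estimated as margins, for example with −0.5/+0.5 coding.

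The cost is wording in a few places and no new data. The price is that claims about one intervention against usual care become openly secondary.

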## Abstract

Recently, a large cluster-randomized controlled trial was designed—Music Interventions for Dementia and Depression in ELderly care (MIDDEL)—to assess the effectiveness of music interventions on depression in care home residents with dementia (ClinicalTrials.gov NCT03496675). To understand the pathophysiological mechanisms, we observed the effect of repeated music interventions on stress in this population since chronic stress was associated with depression and an increased risk for dementia. An exploratory study was designed to assess: (1) changes in hair cortisol concentrations as an indicator of longer-term stress; (2) whether baseline stress is a predictor of therapy outcome; (3) pre- and post-treatment effects on salivary α-amylase and cortisol response as an indicator of immediate stress in 180–200 care home residents with dementia and depressive symptoms who partake in the MIDDEL trial. Insights into mediatory effects of stress to explain the effect of music interventions will be gained. Hair cortisol concentrations were assessed at baseline and at 3, 6, and 12 months along with the Perceived Stress Scale. Salivary α-amylase and cortisol concentrations were assessed at 1, 3, and 6 months. Saliva was collected just before a session and 15 and 60 min after a session, along with a stress Visual Analogue Scale.

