#### 2.10.2. Secondary Study Parameters

In the final model in which MADRS scores at the endpoints (3 and 6 months) are predicted by the therapy group (Gold et al., 2019), baseline stress was added to examine whether chronic stress (HC concentrations; perceived stress) predicts the treatment effect. Secondary study parameters were added to the final model. A description of the effect of amylase response (expected to change at 15 min), cortisol response (expected to change at 60 min), and experienced stress (assessed with the VAS) were provided. Correlation of stress biomarker response (SC and SAA levels at T3 and T6, pre-post treatment) and change in MADRS score (T3–T0 and T6–T0) were examined. The design was able to account for between-group variation (including differential responses in three groups) and within-group variation (changes in participants between 3 months, 6 months, and baseline).

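### The stress–MADRS change correlations are stated without a treatment-arm term, one is not computable as written, and the analyses described do not support the Abstract's mediation sentence

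*Protocol article*

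**What the plan says.** The Abstract makes a mechanistic promise: "Insights into mediatory effects of stress to explain the effect of music interventions will be gained". Mediation is not one of its three numbered aims, nor one of the objectives at the end of the Introduction.

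Two sentences relate change in stress to change in depression:

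- Section 2.10.2: "Correlation of stress biomarker response (SC and SAA levels at T3 and T6, pre-post treatment) and change in MADRS score (T3–T0 and T6–T0").
- Section 2.11, in the paragraph on hair cortisol and PSS-10: "The analyses included a correlation between stress reduction (at T3, pre-post treatment) and change in MADRS score (T6–T3–T0").

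Section 2.10.2 also describes a regression that includes arm: "In the final model in which MADRS scores at the endpoints (3 and 6 months) are predicted by the therapy group". Baseline hair cortisol and perceived stress enter that model, and then "Secondary study parameters were added to the final model". By sections 2.6.3 and 2.6.4 the secondary parameters are salivary cortisol, salivary α-amylase and the stress VAS.

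Hair cortisol and PSS-10 at 3 and 6 months appear in section 2.10.1 as outcomes, modelled on therapy and baseline stress.

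**The concern.** There are two problems.

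**Definition.** The section 2.11 sentence does not name the stress measure. Its MADRS term, read as a subtraction, is not a change from anything. It could mean T6–T0, T6–T3, T3–T0 or a trajectory over three visits. The reader also cannot tell whether it restates the section 2.10.2 correlation or is a separate hair cortisol/PSS-10 analysis.

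**Confounding by arm.** Neither correlation sentence mentions treatment arm. In a randomised comparison, arm is a common cause of both change scores whenever the intervention works on both. Pooling over arms then produces a correlation from the arm means alone. That is the situation the study hopes for, and in it the statistic cannot separate two parallel effects of music from an effect that runs through stress.

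At stake is how the mechanistic result is read. A positive pooled correlation, set beside the Abstract's sentence, would be taken as support for mediation even if residents whose stress fell most within an arm were no more likely to improve on MADRS.

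**Working it through.** **1. The plan's own figure.** Section 2.9 gives 160 participants after 20% dropout, cluster size 8, ICC at most 0.01, two-sided 2.5%, 80% power and d = 0.51.

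- Design effect = 1 + (8 − 1) × 0.01 = 1.07.
- Effective N = 160 / 1.07 = 149.5.
- Detectable d = 0.509 by noncentral t (0.504 by normal approximation); power at d = 0.51 is 80.2%.

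The figure reproduces and is not disputed. It serves below only as a reference size for the intervention effect. The article gives no figure for the correlations.

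**2. Correlation created by arm means alone.** Set the within-arm correlation to zero and the within-arm SD to 1, and let music shift both variables by d. With v the variance of the arm means per unit d²:

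r = v·d² / (1 + v·d²)

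- Three saliva arms (section 2.1), two active and one control: v = (2/3)(1/3) = 2/9; N = 3 × 50 × 0.8 = 120.
- Four arms, one factor active: v = (1/2)(1/2) = 1/4; N = 160.
- Four arms, both factors active and additive: v = 1/4 + 1/4 = 1/2; N = 160.

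At d = 0.51, d² = 0.2601:

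- Saliva: 0.0578 / 1.0578 = 0.055.
- One factor: 0.0650 / 1.0650 = 0.061.
- Both factors: 0.1301 / 1.1301 = 0.115.

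**3. False-positive rate.** By Fisher's z, the test statistic is centred at atanh(r) × √(N − 3). For the saliva arms this is 0.0547 × √117 = 0.59, so a two-sided 5% test rejects with probability P(Z > 1.96 − 0.59) + P(Z < −1.96 − 0.59), about 0.091. The other cases follow the same way. The values d = 0.3 and d = 0.8 are assumptions added to show the range.

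| d on both variables | Saliva arms, N = 120 | Four arms, one factor, N = 160 | Four arms, both factors, N = 160 |
|---|---|---|---|
| 0.3 | r 0.020; 5.5% | r 0.022; 5.9% | r 0.043; 8.4% |
| 0.51 | r 0.055; 9.1% | r 0.061; 11.9% | r 0.115; 30.5% |
| 0.8 | r 0.125; 27.3% | r 0.138; 41.3% | r 0.242; 87.3% |

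**4. Simulation check.** With 4,000 replicates, clusters of 8, five clusters per arm, ICC 0.01 and d = 0.51, the pooled test rejected in 8.9% of trials in the saliva arms and 31.1% with four arms and both factors active. With arm means removed, mean r was 0.00 and rejection was 4.5% to 5.4% across all settings tried (d = 0, 0.51 and 0.8). At d = 0 the pooled test rejected 4.4% to 4.8%, so clustering at the plan's ICC adds nothing visible.

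If music moves only one of the two variables, the product of the shifts is zero and so is the induced correlation.

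**5. The two sentences side by side.**

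| | Section 2.10.2 | Section 2.11 |
|---|---|---|
| Stress measure | Salivary cortisol and α-amylase | Not named |
| Stress time points | T3 and T6 | T3 only |
| MADRS term | T3–T0 and T6–T0 | T6–T3–T0 |
| Arm term | None stated | None stated |

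Under the saliva reading, section 2.11 disagrees with section 2.10.2 on time points. Under the hair/PSS-10 reading, the pre-post label at T3 does not fit, because section 2.4 has the intervention running for six months and T3 is mid-course. The MADRS term is undefined on either reading.

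**6. What could bear on mediation.** Section 2.10.1 gives the effect of music on chronic stress. The other half would be the relation of post-baseline stress to MADRS given arm. Hair cortisol and PSS-10 enter the MADRS model only at baseline, and section 2.3 places randomisation after baseline assessment, so those values cannot mediate. The parameters added later are the saliva and VAS measures, which concern immediate stress in three arms.

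**The case against.** The strongest reply is that section 2.10.2 already contains an arm-conditional analysis: it adds the secondary parameters to a MADRS model that includes therapy group. This stands. A reader might infer that the mediation promise rests entirely on unadjusted correlations, and the text does not support that. What the sentence leaves open is narrower: it states no mediation estimand and does not reach post-baseline hair cortisol or PSS-10.

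A reader might also infer that the two correlation sentences flatly contradict each other. That is not established. The section 2.11 sentence sits in the hair cortisol/PSS-10 paragraph and may be a separate analysis. If so, stress at T3 against a MADRS change reaching T6 would be partly time-ordered.

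The study is exploratory throughout, mediation is not a listed aim, and an article can leave the adjustment of a correlation to a fuller plan. Section 2.10.2 also says "The design was able to account for between-group variation (including differential responses in three groups"), which shows that arm differences were in view. But that describes the design and is not tied to the correlations, and the confounders listed in the Discussion do not include arm. Condensation explains a missing detail. It does not explain an expression that cannot be computed, or a promise in the Abstract with no analysis matching it.

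Finally, the bias may be small. In the saliva arms at d = 0.51 it is: r is about 0.055. Rates above 40% require an assumed 0.8 SD shift on both variables, which the document does not give, and should not be read as the expected error.

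**Conclusion.** The concern holds in limited form. The section 2.11 correlation is not computable as written, and its relation to the one in section 2.10.2 is unclear. Both are stated without arm, and a pooled correlation is biased away from zero when music affects both variables. At d = 0.51 on both, false positives at a 5% test are about 9% in the saliva arms, about 12% with four arms and one factor active, and about 31% with both active. Conditioning on arm brings this back to about 5%. The Abstract's mediation sentence is not supported by the analyses described.

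The sizes rest on equal shifts in both variables, unit within-arm SD, additive factor effects, equal arms, and a 5% level for the correlation, which the article does not state. The d of 0.51 is the plan's detectable effect for its main comparisons, borrowed here for MADRS change as well. Whether a definition could be picked after seeing results cannot be judged from the article, since a fuller plan may fix it. This is worth correcting, but it does not touch the co-primary comparisons.

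**What to change.** 1. Reconcile sections 2.10.2 and 2.11. Say whether they describe one analysis or two, name the stress measure in each, and replace the three-point MADRS expression with a computable quantity. One example is stress change T3–T0 against MADRS at T6 with baseline MADRS as a covariate, which also gives a time order.
2. Estimate each stress–MADRS association conditional on GMT, RCS and the baseline values, allowing for care home unit. In the saliva analyses, condition on the three arms sampled.
3. Label these results exploratory and associational.
4. Soften or remove the mediation sentence in the Abstract unless a mediation analysis is specified. A formal product-of-coefficients analysis is optional. With about 20 care home units its intervals would be wide, and it would have to state its assumption of no unmeasured confounding.

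The cost is some rewording, slightly more analysis work on measurements already planned, and a more modest mechanistic claim. The Data Availability statement says data are still to be collected, so the definitions can be settled before results are seen.
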